**Methods:**

This hybrid type II cluster randomized effectiveness implementation trial (eSMART-TC) aims to examine the effects of interactive assistance for SME management on health and implementation outcomes. We will provide interactive assistance to employers and health managers for 6 months, aiming to promote the utilization of reimbursed smoking cessation treatments by public health insurance and to implement smoke-free workplaces. The intervention will consist of three strategies: supporting employees through campaigns, tailored ongoing facilitation, and ensuring executive engagement and support. The primary health and implementation outcomes will be salivary cotinine-validated 7-day point-prevalence abstinence rate, and the adoption of two recommended measures (promoting utilization of smoking cessation treatment and implementing smoke-free workplaces) 6 months after the initial session, respectively. Other outcomes for implementation (e.g., penetration of smoking cessation clinic visits), health (e.g., salivary cotinine-validated 7-day point-prevalence abstinence rate at 12 months), and process (e.g., adherence and potential moderating factors) will be collected via questionnaires, interviews, logbooks, and interventionists’ notes at 6 and 12 months. An economic analysis will be undertaken to assess the cost-effectiveness of the implementation interventions at 12 months.

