## Background

Smoking is the most preventable risk factor for all-cause mortality in Japan. Although the overall smoking prevalence continues to decline over time, 16.7% of Japanese adults (27.1% men and 7.6% women), including 31.8–36.5% of men aged 30–50 years, were smokers in 2019 [1]. Additionally, owing to population aging and the pervasive health effects of smoking, the number of deaths per year due to smoking increased from approximately 129,000 in 2007 to approximately 190,000 in 2019 [2, 3].

In Japan, the “Standard Procedures for Smoking Cessation Treatment” at registered medical institutions has been provided as an evidence-based intervention under health insurance coverage since 2006. The reimbursed treatment program comprises five treatment sessions over a 12-week duration. Nicotine patches or varenicline could be prescribed during the treatment period. The abstinence rate was approximately 60% when the treatment session finished (including those who dropped out during the process) and approximately 27.3% 9 months after [4]. Despite being the most effective method for smoking cessation available in Japan [5], less than 20% of smokers who quit have used the treatment [6], mainly because of lack of access (only 15% of medical facilities offer smoking cessation treatments) or media campaigns to promote the use of such treatments [7].

The workplace is an ideal setting to reach people of diverse ages and sociodemographic statuses, with or without access to healthcare [8]. It offers a place to provide smoking cessation support and motivate employees to connect with more effective smoking cessation treatments, such as outpatient clinics [9]. Furthermore, a meta-analysis reported that a smoke-free policy in the workplace reduces not only secondhand smoke among employees, but also smoking prevalence by 3.8% [10]. Currently, tobacco control measures in the workplace have not been sufficiently implemented in Japan, especially in small- and medium-sized enterprises (SMEs) where resources are limited. For instance, according to a survey of SMEs in Japan, only 20% of enterprises were engaged in health promotion activities [11], and a national survey showed that the implementation rate of comprehensive smoke-free policies was lower than that of large companies [12].

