#### Cost-related outcomes

The cost-effectiveness of workplace smoking cessation will be estimated as the incremental cost per quit in the intervention group versus the control group over the intervention and follow-up periods (12 months after the initial session). The cost component accounts for three categories: (1) the cost of implementing tobacco control measures in the workplace, (2) employees’ direct medical costs during the study period, and (3) workers’ lost productivity.

The cost of implementing the measures includes the amount of time spent by employers and health managers on implementing the measures, converted into labor costs using the average salary level for the relevant age group in Japan, as well as cost for incentives, including cost assistance schemes for smoking cessation treatments, and the implementation of smoke-free policies. Employees’ direct medical costs consist of medical treatment costs (calculated from the total number of points in the monthly medical fee schedule) and medical expenses (calculated from the monthly total of the medical remuneration statement). Workers’ lost productivity will be estimated based on absenteeism and presenteeism. Absenteeism is the loss of productivity due to absence from work; the amount of labor cost loss will be calculated by converting the number of days of absence from work owing to sickness (from the questionnaire) into labor costs at the average salary level for the relevant age group in Japan. Presenteeism refers to the loss of productivity at work owing to an illness and performing at lower levels than usual. The amount of labor cost loss will be calculated by converting relative presenteeism [i.e., a ratio of actual performance to the performance of most workers at the same job (possible performance) from the World Health Organization Health and Work Performance Questionnaire, Japanese edition] into labor costs at the average salary level for the relevant age group in Japan.

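### Employer subsidies for insured cessation treatment are costed alongside medical costs built on total fee points, with no offset, so subsidised insured courses can be partly counted twice in the cost per quit

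*Protocol article*

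**What the plan says.** The Cost-related outcomes section names three cost categories: workplace implementation, employees' direct medical costs, and lost productivity.

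- **Category 1 (implementation)** covers staff time, smoke-free measures and "cost for incentives, including cost assistance schemes for smoking cessation treatments". Under Cost-related data, its source is the health managers' logbooks.
- **Category 2 (direct medical costs)** has two items. The first, the cost of treatment, is "calculated from the total number of points in the monthly medical fee schedule". The second is taken from each month's total on the claim statement. The source of both is the insurer's database, supplied as enterprise-level means.

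The last part of Statistical analysis divides the between-arm difference in cost per smoker by the difference in quits. It mentions no offset between categories, and no costing perspective is named.

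The Background says that the clinic programme "has been provided as an evidence-based intervention under health insurance coverage since 2006". The Abstract describes the intervention as "aiming to promote the utilization of reimbursed smoking cessation treatments by public health insurance".

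**The concern.** A clinic course under public insurance generates a fee, and that fee is in the claims. If an employer scheme repays the employee for part of it, no further resource is used; the payment only changes who bears the cost. Counting the whole fee in category 2 and the repayment in category 1 counts that part twice.

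No single perspective justifies counting both. An employer's account would include the subsidy but not the insurer's claims. An insurer's account would include its claims but not the employer's subsidy. A societal account, which the three categories together most resemble, would include the fee once and treat the subsidy as a transfer.

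The cost per quit at 12 months is the Aim 3 result. The intervention arm is helped to run a campaign with optional incentives and is steered towards clinics, so any overlap would be expected to fall mainly there and to make the programme look dearer. The planned sensitivity analyses vary the inputs; they do not remove an item counted twice. The primary health and implementation outcomes are unaffected.

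**Working it through.** The article states no cost, subsidy or cost-per-quit figure, so there is nothing to reproduce. The check is an accounting identity, followed by an illustration in index units.

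**Inputs**

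- F, full fee of a course: not given. Set to 100 units.
- s, share of the fee repaid by the employer: not given. Assumed 0, 0.1, 0.2 or 0.3.
- u, subsidised insured courses per smoker, intervention minus control: not given. Assumed 0.05, 0.10 or 0.20.
- dq, difference in quit rates: 0.133 − 0.037 = 0.096, from Sample size and power calculations. These are 6-month planning rates, used here as a stand-in because Aim 3 is at 12 months.

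**Step 1, one subsidised insured course.** Category 2 contributes F if the points total is gross. Category 1 contributes sF. The sum is F + sF = F(1+s); the resource used is F; the excess is sF. With F = 100, the course is counted as 100, 110, 120 or 130 for s = 0, 0.1, 0.2 or 0.3.

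**Step 2, between-arm difference per smoker.** The excess is s × F × u.

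**Step 3, cost per quit.** The overstatement is s × F × u / dq. For example, 0.1 × 100 × 0.05 / 0.096 = 0.5 / 0.096 = 5.2, and 0.3 × 100 × 0.20 / 0.096 = 6 / 0.096 = 62.5.

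| s | u = 0.05 | u = 0.10 | u = 0.20 |
|---|---|---|---|
| 0 | 0 | 0 | 0 |
| 0.1 | 5.2 | 10.4 | 20.8 |
| 0.2 | 10.4 | 20.8 | 41.7 |
| 0.3 | 15.6 | 31.2 | 62.5 |

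Because F = 100, each entry is a percentage of one course fee per additional quit. On these assumptions the range is 0 to 62.5%. If the claims amount is net of the employee's share and the subsidy pays only that share, every entry is zero.

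**The case against.** The strongest reply is that this is a missing detail rather than an error. The article defers detailed methods for secondary outcomes, which include costs, to an analysis plan that is not shown, and a rule on transfers could be there. That is fair as to what the final analysis may do. It does not change what the article itself fixes: both items are listed as components of the cost, and the formula combines costs without an offset.

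Other replies stand and limit the point:

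- A reader might infer that part of every clinic course is counted twice. The documents do not support this. The Intervention section makes incentives optional, and only a course that is both insured and subsidised can overlap.
- The schemes are not restricted to insured care. Over-the-counter products are the next option offered to smokers; a subsidy for these is assumed to be outside the claims and would not overlap.
- That the points total is gross is an inference from the word total. The article does not say whether the employee's share is included.
- A reader might attach a sum of money to the bias. The article gives no prices, shares or uptake, so any such sum would rest on outside figures.
- The net direction of error in the treatment cost also depends on scaling. Category 2 may arrive as a mean over all employees. If that mean were used unscaled as a cost per smoker, at the planning value of 30% smokers only 0.3F of a smoker's course would enter, and adding a subsidy of 0.3F gives 0.6F, which is below F. That would be a separate error; it would not make the subsidy an additional resource.

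**Conclusion.** The point holds in conditional form. Followed as written, the costing counts the subsidised part of an insured course twice, provided that the points total is gross of the employee's share and that some employers subsidise insured clinic care. The subsidy component then overstates the cost per quit by s × F × u / dq. The size cannot be derived from the documents; it is zero if either condition fails, and the tabulated values are illustrations only. The upward direction assumes more subsidised insured courses per smoker in the intervention arm (u above zero) and a positive difference in quit rates. This is a minor matter, confined to Aim 3, but worth settling because the remedy is cheap.

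**What to change.** State one costing perspective and confirm whether the claims amounts include the employee's share. If they do, the base case should exclude from category 1 any employer subsidy for insured clinic treatment, or net it off category 2. Exclusion is simpler, since the claims arrive as enterprise-level means. Keep subsidies for products that do not appear on claims. Where the logbooks do not separate the two kinds, report the cost per quit with and without the subsidies.

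This is a costing rule and needs no new data source. The cost is that some logbook entries may have to be clarified with health managers. Trial status says that the 12-month evaluation was under way in April 2023, so it is late to redesign the logbook, but that data analysis had not begun, so at that point the rule could still be set before results were seen.

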### Data collection procedures

A multi-method approach will be used to collect data. Data collection methods will include questionnaires (employee questionnaire, workplace questionnaire, and workplace tobacco control checklist), biochemical tests, semi-structured interviews, health managers’ logbooks, interventionists’ notes, and cost-related data from health insurance database.

#### Questionnaire

Data from the employee questionnaires will be collected electronically using the electronic data capture system ViedocMe (Viedoc Technologies, Sweden) established by the data center. The QR code of the URL of this survey form will be printed and distributed to each employee, along with their individual account ID and password. During the predefined questionnaire response period, employees will log in using their individual account ID and password on the web page or by using an application on a smartphone or tablet device and then complete the survey. Once logged in, a check box will ask whether the participants agree to complete the survey, after an introduction to this project and the survey. If an employee selects the “Disagree” box, the survey form will be closed. If enterprises desire, printed paper responses will also be accepted. Saliva will be collected by mail from employees who report they have not smoked in the past 7 days at the 6- and 12-month follow-up [34]. Data from the workplace questionnaire and workplace tobacco control checklist will be collected electronically using survey applications, such as Google Forms and Microsoft Forms.

#### Biochemical test

For saliva collection, employees will receive a kit with instructions from a health manager at the workplace and provide verbal consent via telephone to the research staff prior to saliva collection. Samples returned to the research team will be stored in a refrigerator until they are mailed to an independent laboratory specializing in the analysis of biological samples. For employees who report using a nicotine patch or gum within 7 days of the salivary cotinine measurement date, we will ask them to measure expired air CO concentrations using a Smokerlyzer (Harada Industry, Osaka, Japan) online and show the results to the research staff through a screen.

#### Semi-structured interviews

Semi-structured interviews will be conducted only for intervention groups. The interviews with the employer and health managers will be conducted together in the same place at 6 months, while interviews with employees at 6 months will be conducted separately. Semi-structured interviews at 12 months will be scheduled for health managers only but will be conducted optionally if the results of the interview suggest that additional information is required from employers or employees. An interview guide will be developed with open-ended questions. For employers and health managers, the guide will cover acceptance and appropriateness of this intervention, the fidelity of tobacco control activities recommended during the intervention, and also covers the process of normalization of tobacco control measures in the worksite based on the Normalization Process Theory [35]. The guide will cover responsiveness, acceptance, and perceived context (all within potential moderators in the fidelity model) for employees. Each interview will last approximately 30–60 min. Interviews and focus groups will be conducted in Japanese, audio recorded, transcribed, and verified for accuracy. The interviewees will receive a coupon card (Quocard) for JPY 1000 as a reward.

#### Other data sources

Health managers will fill their logbooks in a timely manner whenever they take any action regarding tobacco control measures during the intervention and follow-up period, in both intervention and control groups.

#### Cost-related data

Health managers’ logbooks will be used to estimate the costs of implementing tobacco control measures in the workplace. For data on the direct medical costs of employees during the study period, the mean values for all employees or the smoking population in each SME will be obtained from the health insurance database at JHIA headquarters after obtaining each SMEs’ employer agreement. Finally, an employee questionnaire will be used to assess workers’ lost productivity. All data will be stored securely and will only be accessible to the research team and data manager.

### Sample size and power calculations

The purpose of this study is to test the effectiveness of an intervention that can be disseminated to small- and medium-sized enterprises with limited resources. To achieve this goal, we considered the intervention to be effective if it produces an abstinence rate that is equal to or greater than that in a previous study on similar interventions in a Japanese workplace setting [16]. Thus, we assumed the 7-day point-prevalence abstinence rate to be 13.3% for the intervention group 6 months after the intervention begins.

The smoking cessation percentage of the control group was estimated to be 3.7%. As a breakdown of the 3.7%, the 2.3% under natural behavior change was based on the difference in the average smoking rates between fiscal year 2018 and 2019 for companies belonging to the JHIA (only among companies with 10–999 employees), and the 1.4% as an impact of the revision of the Health Promotion Act was based on the proportion of enterprises that said they would promote tobacco control measures if the Health Promotion Act was revised, according to a survey of approximately 6,000 enterprises nationwide [36]. Thus, we assumed the abstinence rate in the control group would be higher than the 2.5% in the control group who received only information in the previous intervention study. [16]

With a mean of 15 smokers per cluster (assuming 50 employees and a smoking proportion of 30% in each SME) and an intra­class correlation of 0.05 based on a previous cluster randomized study in the workplace [37], which provides a design effect of 1.70, a sample size of 240 smoking employees within 16 clusters per group will be required with a two-sided significance level of 5% and 80% power. Given a 10% loss to follow-up due to unexpected employee turnover, resignation, or retirement, the planned sample size is at least 264 smokers in 18 clusters per group.

### Statistical analysis

The primary analysis for the primary outcome will be conducted on an intention-to-treat basis, that is all randomized participants who respond as being current smokers at baseline and have the biochemically confirmed 7-day point-prevalence abstinence data at 6 months will be included in the analysis and will be analyzed according to the group to which they were allocated. The primary analysis will exclude the participants lost to follow-up and no imputation of missing data will be performed; however, imputing missing data may be considered to account for all randomized participants in the sensitivity analysis. For the primary outcome, the biochemically confirmed 7-day point-prevalence abstinence rate at 6 months will be compared between the intervention and control groups, and the difference in the abstinence rates with 95% confidence intervals (CIs) will be estimated. A generalized estimating equation (GEEs) method with an identity link and an exchangeable correlation structure will be used. Robust variance will be used for hypothesis testing and estimation. The allocation factors of the number of employees and the implementation of a comprehensive smoke-free policy at the workplace will be adjusted in the GEE model. A two-sided *P* value of 0.05 or less will be considered statistically significant. Because of model convergence issues, we may also consider a logistic regression model with GEEs and an exchangeable correlation structure for hypothesis testing and estimating odds ratios with 95% CIs. Secondary outcomes, including implementation, and process, health, and cost-related outcomes, will also be analyzed. Detailed methods for the secondary outcomes and sensitivity analyses will be specified in the Statistical Analysis Plan before the study data are fixed.

Regarding adherence content, which will be measured in the intervention group only, we will conduct paired t-tests to examine pre- versus post-intervention changes in responses of the adherence measured by the workplace tobacco control checklist.

The incremental cost per quit will be estimated as the cost per smoker in the intervention group minus the cost per smoker in the control group divided by the incremental quit between the intervention and control groups. Probabilistic and deterministic sensitivity analyses will be performed to quantify the uncertainties associated with the input parameters and to assess the robustness of the base case. The deterministic analysis will assume a percentage variation of respective cost parameters from the base case. Monte Carlo simulation will be applied to conduct probabilistic sensitivity analysis by varying the input parameters based on the appropriate distributions.

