### Study population

The study population will include intervention and evaluation targets. The intervention targets will be an employer and a health manager at each participating SME. In cases where it is difficult for an employer to participate, it will be possible for a person in a managerial position to implement measures within the enterprise to participate in the study as the equivalent of an employer.

The evaluation target will include all employees of the participating SMEs, in addition to the intervention targets. Thus, for employee-level analysis, all employees of randomized enterprises who meet the eligibility criteria will be included in the analysis.

Inclusion criteria for employers:An employer or someone with influence on decision-making at eligible SMEs.Aged ≥ 20 years.Able to read, write, and understand Japanese.

Inclusion criteria for health managers:Involved in fostering health management and promotion among employees at eligible SMEs.Aged ≥ 20 years.Able to read, write, and understand Japanese.

Exclusion criteria for employers and health managers:Those who have already decided to move or change jobs within the next year and plan to leave their current affiliation.Those who are deemed unsuitable by the JHIA branch office for participating in this study.

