#### Health outcomes

The primary health outcome will be the salivary cotinine-validated 7-day point-prevalence abstinence rate 6 months after the initial session, according to the Russell Standard [29]. Abstinence rate will be assessed by self-reporting using an employee questionnaire with the following questions: “Have you smoked even one mouthful of tobacco [including all cigarettes, (cigarettes rolled in paper, heated, and other types)] in the last seven days?” Seven-day point-prevalence is defined as salivary nicotine-confirmed self-reported tobacco cessation in the last 7 days (response of “no” to the above question), and a cotinine concentration of 15 ng/ml or less will verify self-reported smoking abstinence [30]. A Smokerlyzer will be used to measure expired air carbon monoxide concentrations, with a cut-off point of six parts per million if self-reported quitters report using a nicotine patch or gum within 7 days of the salivary cotinine measurement date [31]. If an employee’s self-reported smoking abstinence does not match the biochemical measurement, the employee will be classified as a smoker.

Other health outcomes include the salivary cotinine-validated 7-day point-prevalence abstinence rate 12 months after the initial session, 30-day point-prevalence abstinence rate at 6 and 12 months, 3-month point-prevalence abstinence rate at 6 and 12 months, 6-month point-prevalence of abstinence rate at 12 months, the proportion of quit attempts at 6 and 12 months, and the number of cigarettes or capsules at 6 and 12 months among employees who report being smokers at the baseline survey. Among employees who smoke and declare to quit during the intervention period in the intervention group, the 3 months prolonged abstinence rate at 6 and 12 months, and 6 months prolonged abstinence rate at 12 months will be measured. In addition, we will assess the proportion of nicotine patches and gum use in the past 6 and 12 months measured at 6- and 12-month follow-ups, respectively, among employees who smoke at baseline.

Furthermore, the mean values and response rates for basic health check-up items (medical interview sheet, physical measurements, blood pressure, blood lipids, liver function, blood glucose, and urine) in all employees or in the smoking population will be obtained from the JHIA headquarters after each SMEs’ employer agrees.

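### The primary analysis is labelled intention-to-treat but is a complete-case analysis in which inclusion can depend on the outcome, giving a bias of unknown size and direction

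*Protocol article*

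**What the plan says.** The Statistical analysis section of the protocol article presents the primary analysis as intention-to-treat and defines the analysed group as "all randomized participants who respond as being current smokers at baseline and have the biochemically confirmed 7-day point-prevalence abstinence data at 6 months". It adds: "The primary analysis will exclude the participants lost to follow-up and no imputation of missing data will be performed". The only analysis of everyone randomised is optional: "imputing missing data may be considered to account for all randomized participants in the sensitivity analysis".

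The Study population section reads differently: "for employee-level analysis, all employees of randomized enterprises who meet the eligibility criteria will be included in the analysis".

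Three other statements determine who can have a verified outcome:

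- Questionnaire section: "Saliva will be collected by mail from employees who report they have not smoked in the past 7 days", at the 6- and 12-month follow-ups.
- Biochemical test section: employees must "provide verbal consent via telephone to the research staff prior to saliva collection". Recent users of a nicotine patch or gum are asked for an expired-air CO reading instead.
- Health outcomes section, on a claimed quitter whose test disagrees: if "self-reported smoking abstinence does not match the biochemical measurement, the employee will be classified as a smoker". The article gives no rule for a claimed quitter with no test result.

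The Statistical analysis section defers the detail of secondary outcomes and sensitivity analyses to the SAP. The primary set and the decision not to impute are stated in the article itself.

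**The concern.** The label and the definition do not agree. An intention-to-treat set is fixed at randomisation. This one depends on something observed six months later, and whether it is observed is linked to the answer. Four kinds of baseline smoker can be told apart at 6 months:

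1. Reports smoking: no test is requested. Taken literally, this person has no biochemical data and would be excluded. That cannot be meant, since the planning rates are 13.3% and 3.7%. On a sensible reading the person counts as a smoker on self-report alone.
2. Reports abstinence and passes the test: abstinent.
3. Reports abstinence and fails the test: smoker.
4. Reports abstinence and gives no sample, or does not answer at all: removed from numerator and denominator.

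A false claim that is tested therefore counts against the arm, while a false claim that is never tested disappears. A true quitter who skips the telephone consent or the sample disappears too. Since follow-up may also differ between unblinded arms, the primary comparison loses part of the protection that randomisation gives.

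**Working it through.** **The plan's own figure first.** The inputs, from Sample size and power calculations, are 13.3% v 3.7%, two-sided 5%, 80% power, 15 smokers per cluster and ICC 0.05.

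- Design effect = 1 + (15 − 1) × 0.05 = 1.70, as stated.
- The usual two-proportion formula gives 132 per arm. 132 × 1.70 = 224.4, and 224.4 / 15 = 14.96 clusters.
- Adding one cluster per arm (my assumption about how it was done) gives 15.96, so 16 clusters and 16 × 15 = 240, as stated.
- 240 × 1.10 = 264, as stated. 240 / 0.9 = 267, which 18 × 15 = 270 covers.

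The sample size is not at issue. The 10% loss is attributed to employees leaving the enterprise. It is not split by arm and makes no separate allowance for unanswered questionnaires or unreturned saliva.

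**What the complete-case analysis would show.** Let p be the true rate among all baseline smokers, taken as 13.3% and 3.7% (difference 9.6 points). Let q be the share of true quitters, and s the share of true smokers, whose outcome is missing. Then

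complete-case rate = p(1 − q) / [p(1 − q) + (1 − p)(1 − s)].

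If everyone missing smokes and m is the share of the arm that is missing, this reduces to p / (1 − m). If only true quitters are missing, it reduces to p(1 − q) / (1 − pq). The only loss figure in the article is 10%; every other value below is an assumption.

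| Who is missing | Intervention | Control | Difference (true 9.6) |
|---|---|---|---|
| Smokers, 10% each arm | 13.3/0.90 = 14.8% | 3.7/0.90 = 4.1% | 10.7 |
| Smokers, 20% each arm | 13.3/0.80 = 16.6% | 3.7/0.80 = 4.6% | 12.0 |
| Smokers, 10% v 30% | 13.3/0.90 = 14.8% | 3.7/0.70 = 5.3% | 9.5 |
| Smokers, 5% v 30% | 13.3/0.95 = 14.0% | 3.7/0.70 = 5.3% | 8.7 |
| 20% of true quitters, each arm | 10.64/0.9734 = 10.9% | 2.96/0.9926 = 3.0% | 7.95 |
| 10% of quitters and 10% of smokers | 13.3% | 3.7% | 9.6 |

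When all missing people smoke, the change in the difference is p₁m₁/(1 − m₁) − p₂m₂/(1 − m₂). The difference is therefore understated once the control arm's odds of loss exceed 13.3/3.7 = 3.6 times those of the intervention arm.

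**No true effect.** Take 3.7% in both arms, with all missing people smoking. Loss of 30% in one arm and 10% in the other gives 3.7/0.70 = 5.3% and 3.7/0.90 = 4.1%. That is a spurious 1.2 points in favour of whichever arm loses more. Equal loss gives no spurious difference.

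**The case against.** A reader might infer that both abstinence rates and their difference are bound to be inflated. The documents do not support that. It requires that those missing mainly smoke and, for the difference, that control loss is not far above intervention loss. The table shows the result moving either way, and no bias if missingness is unrelated to smoking. At the one loss figure in the article, the inflation under the worst-case assumption that everyone missing smokes is about 1.1 points.

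Three further inferences also fail.

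- Health managers hand out the saliva kits, but the Biochemical test section does not limit this to one arm, and Table 2 marks the cotinine outcome as collected in both groups. Kit hand-out is no evidence of an arm difference.
- The Discussion says only that allocation to control might reduce the motivation of employers and health managers. It predicts nothing about employees' responses. If control loss were higher, and those lost smoked, the difference would move against the intervention.
- A literal reading that keeps only tested claimants, with a rate near 100%, is ruled out by the planning rates. The article gives no test-failure rate to support it either.

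It can also be said that the Study population sentence covers all employees, non-smokers included, and so cannot define the smoker analysis; that sensitivity methods are left to an SAP not shown here; and that counting all missing people as smokers is itself a crude imputation. These points have weight. The two sections sit poorly together rather than contradict each other outright, and detailed sensitivity methods are not a gap. The label, the complete-case set and the no-imputation rule are nevertheless fixed in the article, and none of these points removes them.

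**Conclusion.** The concern holds in this limited form: the primary analysis is complete-case under an intention-to-treat label, inclusion can depend on the outcome, and the article has no rule for a claimed quitter without a test. In the scenarios above, a true difference of 9.6 points would be reported as anything from 7.95 to 12.0. Those figures rest on the planning rates being true among all baseline smokers and on assumed loss patterns, apart from the 10%. The documents do not allow the direction to be settled. The point matters because it governs the primary estimate and can be corrected at little cost before the data are fixed.

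**What to change.** Before data lock, and in the SAP:

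- Define the primary set as all baseline smokers in randomised enterprises, analysed as allocated, and reconcile the Study population and Statistical analysis sections.
- State that a self-reported smoker counts as not abstinent without a test.
- Count a self-reported abstainer without a valid cotinine or CO result as not abstinent, in line with the existing mismatch rule.
- Replace the optional imputation with a firm, pre-specified analysis of all baseline smokers: 6-month non-responders as not abstinent, plus multiple imputation that allows for clustering and arm-specific missingness. Making missing-as-smoking the sole primary rule for non-responders is more debatable. It should at least be one of the firm analyses.
- Keep the complete-case analysis if wanted, but do not call it intention-to-treat.

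The cost is wording; no new data are needed, and at first submission (April 2023) data cleaning and analysis had not begun. Reported rates would fall somewhat. If 13.3% and 3.7% are complete-case rates, counting 10% missing as smoking gives 13.3 × 0.9 = 11.97% v 3.7 × 0.9 = 3.33%, a difference of 8.64 points. Power is about 82% with 264 per arm and design effect 1.70. At an assumed 20% it is 10.64% v 2.96% and about 77%.

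The recoding does not cure non-return by true quitters. With 20% of them untested the difference becomes 13.3 × 0.8 − 3.7 × 0.8 = 7.68 points, against 7.95 in the complete-case analysis. Missing-as-smoking can also mislead when loss differs by arm, which the imputation analyses would show.
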